### Secondary objective(s)

- To assess Patient satisfaction (on a scale of 1-10) in both groups
- To assess feasibility of outpatient recovery after standard bariatric surgery by evaluating recruitment rate, adherence to protocol and randomization, and the amount of missing data.

|                                                                                                                    |              |                        |                  |                    |
|--------------------------------------------------------------------------------------------------------------------|--------------|------------------------|------------------|--------------------|
| Title: Clinical Investigation Plan                                                                                 |              | Author: [name] |                  | Philips restricted |
| DocID: ICBE-2-36455                                                                                                | Version: 3.0 | Date: 2020-DEC-08      | Status: Approved | Page: 20 of 44     |
| This document is based on Philips Research Template: Clinical Investigation Plan, ID: QR-TEM-57, Date: 2019-Mar-21 |              |                        |                  |                    |

- To evaluate the percentage and total number of false-positive notifications from the Healthdot system.
- To evaluate the percentage of missed events (i.e. false negatives) from the Healthdot system.
- To evaluate the total number of missed minor events from the Healthdot system.
- To evaluate the outcome of patients who choose HD versus patients who were randomized to HD on a combined outcome measure as defined for the primary endpoint.
- To compare the number of adverse events in both groups
- To compare the use of pain medication during day of surgery until evening in both groups.
- To compare the clinical decisions made on basis of remote monitoring with the Healthdot system, to decisions which also include information from a telephone consultation
- To evaluate the impact of outpatient recovery after standard bariatric surgery and the Healthdot on patient and health professional satisfaction
- To evaluate the costs involved with outpatient recovery after standard bariatric surgery supported by Healthdot.
- To evaluate usability of the visualization of Healthdot data on the Guardian dashboard.

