### Secondary hypotheses

- Patient satisfaction >6 points (on a scale of 1-10) is not significantly different between both groups
- Outpatient recovery after standard bariatric surgery with Healthdot monitoring is feasible based on evaluating recruitment rate (>60% of patients), adherence to protocol (>75% of patients), and the amount of missing data (<10%).
- False-positive notifications from the Healthdot system are lower than 10% of notifications per patient.
- Missed events (false negatives) i.e. there was no notification from the Healthdot system when the patient needed to go to the hospital, are lower than 5% of all notifications.
- Missed minor events occur less than five times per patient. Missed minor events are defined as when there was no notification from the Healthdot system and the patient contacted the hospital, but there was no need for the patient to visit the hospital.
- The outcome of patients who choose HD versus patients who were randomized to HD on a combined outcome measure as defined for the primary endpoint are the same.
- The number of adverse events is not significantly different in both groups.

|                                                                                                                    |              |                        |                  |                    |
|--------------------------------------------------------------------------------------------------------------------|--------------|------------------------|------------------|--------------------|
| Title: Clinical Investigation Plan                                                                                 |              | Author: [name] |                  | Philips restricted |
| DocID: ICBE-2-36455                                                                                                | Version: 3.0 | Date: 2020-DEC-08      | Status: Approved | Page: 21 of 44     |
| This document is based on Philips Research Template: Clinical Investigation Plan, ID: QR-TEM-57, Date: 2019-Mar-21 |              |                        |                  |                    |

- The amount of pain medication during day of surgery until evening in both groups is not significantly different.
- Clinical decisions made on basis of remote monitoring with the Healthdot system do not change in more than 5% of cases when information from a telephone consultation is also included in the decision making process.

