- Patient and health professional satisfaction (on a scale from 1-10) for outpatient recovery after standard bariatric surgery with the Healthdot are equal or higher than for current treatment.
- The costs involved with outpatient recovery after standard bariatric surgery supported by Healthdot is less than the cost involved with the current recovery path, in the period up to 7 days after surgery.
- The usability of the visualization of Healthdot data on the Guardian dashboard is scored good (at least 4 out of 5).

These hypotheses will be accepted or rejected based on the outcome of this clinical investigation.

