## 6 CLINICAL INVESTIGATION DESIGN

### 6.1 General

This clinical investigation is designed as a single center patient preference trial in a tertiary hospital in the Netherlands. We will test for non-inferiority of the outcome of the outpatient recovery after standard bariatric surgery compared to the current treatment, as well as evaluate the feasibility of the outpatient recovery after standard bariatric surgery.

To avoid bias, patient preference for either the current recovery path (group B) or the outpatient recovery (group A) after standard bariatric surgery is noted to be able to include the preference factor in the analysis. The patients that don't have a preference will be randomly assigned. The number of patients included in each group will be equal.

The primary endpoint of the study is the combined outcome measure, based on the following:

- Mortality
- Severe postoperative complications (Clavien-Dindo IIIb or higher)
- Readmission (at least one night in hospital)
- Mild complications (Clavien-Dindo II and IIIa)
- Prolonged length of stay (3 days or more in hospital)

within 30 days after primary surgery.

The secondary endpoints of the study are:

- Patient satisfaction >6 points (on a scale of 1-10)
- Percentage of patients recruited for the outpatient recovery after standard bariatric surgery group
- Percentage of patients with full adherence to protocol and randomization
- Percentage of missing data

|                                                                                                                    |              |                        |                  |                    |
|--------------------------------------------------------------------------------------------------------------------|--------------|------------------------|------------------|--------------------|
| Title: Clinical Investigation Plan                                                                                 |              | Author: [name] |                  | Philips restricted |
| DocID: ICBE-2-36455                                                                                                | Version: 3.0 | Date: 2020-DEC-08      | Status: Approved | Page: 22 of 44     |
| This document is based on Philips Research Template: Clinical Investigation Plan, ID: QR-TEM-57, Date: 2019-Mar-21 |              |                        |                  |                    |

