- Percentage of false positive of the positive notifications from the Healthdot system
- Total number of false positive of the positive notifications from the Healthdot system
- Total number of false negative notifications from the Healthdot system
- The outcome of patients who choose HD versus patients who were randomized to HD on a combined outcome measure as defined for the primary endpoint.
- To evaluate the outcome of patients who choose HD versus patients who were randomized to HD on a combined outcome measure as defined for the primary endpoint.
- Number of adverse events in both groups
- Amount of pain medication taken on the day of surgery in both groups
- Percentage of clinical decisions made based on the Healthdot system, that changed when information from a telephone consultation was also included.
- Patient and health professional satisfaction (on a scale from 1-10) for both the outpatient recovery after standard bariatric surgery group as the current recovery path group
- The costs involved with outpatient recovery after standard bariatric surgery supported by Healthdot and the cost involved with the current recovery path, in the period up to 7 days after surgery.

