| How satisfied are you with the level of care after discharge from the hospital?                                                                                                                 | [figure not shown] | [figure not shown] | [figure not shown] | [figure not shown] | [figure not shown] |            |   |   |   |    |
| What is your overall level of satisfaction?
(1 "not satisfied at all" to 10 "very satisfied")                                                                                                | 1                                                                                   | 2                                                                                   | 3                                                                                     | 4                                                                                     | 5                                                                                     | 6          | 7 | 8 | 9 | 10 |
| Did you find it important that you had the possibility to choose between going home sooner with a sensor or staying a day longer in the hospital without a sensor?                              | No                                                                                  |                                                                                     | Yes                                                                                   |                                                                                       |                                                                                       | Don't know |   |   |   |    |
| Do you have any comments about how you experienced the home monitoring? Do you have any suggestions for improvement?
(Only fill in this question if you did wear the investigational device) |                                                                                     |                                                                                     |                                                                                       |                                                                                       |                                                                                       |            |   |   |   |    |

Table 3: Health care professional questionnaire. Health care professional should circle the selected answer.

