## Statistical design

This study is primarily designed to test for non-inferiority of outpatient recovery compared to regular treatment for bariatric surgery. The outcome measure that we will use for the analysis is a combined measure, based on the following:

- Mortality
- Severe postoperative complications (Clavien-Dindo IIIb or higher)
- Readmission (at least one night in hospital)
- Mild complications (Clavien-Dindo II and IIIa)
- Prolonged length of stay (3 days or more in hospital)

within 30 days after primary surgery.

We choose to use this combined outcome measure since it is in line with other surgical studies [5] making it comparable to literature.

I current practice at Catharina Hospital, Eindhoven, 95% of all bariatric surgery patients do not have any of these events which is considered the textbook outcome here.

We set the following null and alternative hypotheses for proving non-inferiority:

$H_0: p_{\text{regular}} - p_{\text{outpatient}} \geq \Delta$

$H_1: p_{\text{regular}} - p_{\text{outpatient}} < \Delta$

Where  $p_{\text{regular}}$  is the textbook outcome proportion in the regular treatment group, and  $p_{\text{outpatient}}$  is the textbook outcome proportion in the outpatient recovery group. We will use a non-inferiority margin ( $\Delta$ ) of 7%, which is deemed clinically significant by the Principal Investigator. This is also justified by a previous study where the average textbook outcome across bariatric surgery patients in the Netherlands was 88,7% [5] which helps to derive a non-inferiority margin of around 7% to the one seen at Catharina Hospital. We will use an uncorrected chi-squared statistic. Based on the sample size calculation done below an p value of 0.05 will be considered statistically significant. For the interim analysis an alpha correction for multiple testings is applied and a p value of 0.025 will be considered statistically significant.

The secondary endpoints will be analysed statistically in analogy to the primary endpoint by uncorrected chi-squared statistic where deemed appropriate.

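### Patient satisfaction, collected as a 1-10 score, carries two overlapping secondary hypotheses; the one cut at above 6 discards information and becomes easier to accept as power falls

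*Protocol*

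**What the plan says.** In Protocol section 5 the first secondary objective carries no cut-off: "To assess Patient satisfaction (on a scale of 1-10) in both groups". The data are collected the same way. In the patient questionnaire (section 6.4, Follow up, Table 2) the item "What is your overall level of satisfaction" is answered by circling a whole number from 1 to 10.

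Two secondary hypotheses in section 5 then use patient satisfaction:

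- The first applies a cut: "Patient satisfaction >6 points (on a scale of 1-10) is not significantly different between both groups". The matching endpoint in section 6.1 is "Patient satisfaction >6 points (on a scale of 1-10").
- A later one, set against the existing recovery path, does not: "Patient and health professional satisfaction (on a scale from 1-10) for outpatient recovery after standard bariatric surgery with the Healthdot are equal or higher". Its endpoint in section 6.1 is also on the full scale: "Patient and health professional satisfaction (on a scale from 1-10) for both the outpatient recovery" group and the current-path group.

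Section 5 adds that the secondary hypotheses will be accepted or rejected on the study's outcome, and that claims may be derived from them. On analysis, section 7 (Statistical design) says: "The secondary endpoints will be analysed statistically in analogy to the primary endpoint by uncorrected chi-squared statistic where deemed appropriate". For the significance level it says "an p value of 0.05 will be considered statistically significant". No reason is given for the cut at 6. No expected mean, SD or power is given for satisfaction.

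**The concern.** Cutting the score makes 7 the same as 10 and 1 the same as 6. Any patient whose score changes but stays above 6 contributes nothing to the comparison. If most patients score 7 or more, little variation is left for the test.

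For an ordinary superiority question this would only be inefficient. Here the hypothesis is that the groups do not differ significantly, so a non-significant result is the one the sponsor hopes for. A less sensitive endpoint makes that result more likely even when outpatient recovery lowers satisfaction.

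The same questionnaire item also feeds the equal-or-higher hypothesis. The two are different claims and can give different verdicts: the share above 6 may show no significant difference while the mean score is lower in outpatients, or the reverse. The protocol does not say which verdict would be reported as the satisfaction result. Higher satisfaction is the one potential patient benefit named in section 4.

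**Working it through.** **The plan's own figure.** The only sample size stated is for the primary endpoint, and it reproduces with a one-sided 0.05:

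n = (1.645 + 0.842)² × 2 × 0.96 × 0.04 / 0.07² = 6.18 × 0.0768 / 0.0049 ≈ 97 per group.

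It says nothing about satisfaction, for which there is no figure to reproduce.

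**Inputs.** From the protocol: a 1-10 item, a cut at above 6, 100 per group and a level of 0.05. Assumed, because the documents are silent: a normal score rounded and limited to 1-10; regular-group mean 7.5, 8.0 or 8.5; SD 1.0, 1.5 or 2.0; the same SD in both groups; a two-sided test. The loss is set on the scale before rounding. A loss of 0.5 there is 0.40 to 0.50 points in observed means.

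**One case by formula** (mean 8.0 against 7.5, SD 1.5).

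Share above 6: Φ((8.0 − 6.5)/1.5) = 0.8413 against Φ((7.5 − 6.5)/1.5) = 0.7475; difference 0.0938, average 0.7944.

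- SE under no difference: √(2 × 0.7944 × 0.2056 / 100) = 0.0572.
- SE under the alternative: √((0.8413 × 0.1587 + 0.7475 × 0.2525)/100) = 0.0568.
- Chi-squared power: Φ((0.0938 − 1.96 × 0.0572)/0.0568) = Φ(−0.32) ≈ 37%.

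Full score: observed means 7.94 and 7.47, SD 1.42, SE = 1.42 × √(2/100) = 0.201. Power = Φ(0.47/0.201 − 1.96) = Φ(0.38) ≈ 65%.

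**Simulation** (6,000 trials per row, loss of 0.5, 100 per group). The last column covers the Wilcoxon rank-sum test and the t-test.

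| Mean, SD (regular) | Share above 6, regular v outpatient | Chi-squared on above 6 | Full score |
|---|---|---|---|
| 7.5, 1.0 | 84.1% v 69.1% | 71% | 91-92% |
| 7.5, 1.5 | 74.8% v 63.1% | 44% | 61-63% |
| 7.5, 2.0 | 69.1% v 59.9% | 28% | 40-41% |
| 8.0, 1.0 | 93.3% v 84.1% | 56% | 92% |
| 8.0, 1.5 | 84.1% v 74.8% | 38% | 61-62% |
| 8.0, 2.0 | 77.3% v 69.1% | 26% | 39-40% |
| 8.5, 1.0 | 97.7% v 93.3% | 30% | 92% |
| 8.5, 1.5 | 90.9% v 84.1% | 31% | 62% |
| 8.5, 2.0 | 84.1% v 77.3% | 24% | 39% |

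The full score gains about 12 to 62 percentage points. With no true difference, all three tests reject in about 4-6% of trials, so the gain is not bought with false positives.

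**Larger losses, same grid.** For 0.75 points the cut has about 46-98% power and the full score 71% or more. For 1.0 point the cut has about 71% to above 99% and the full score 91% or more.

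**Near the ceiling** (mean 9.0, SD 1.0, loss 0.5): 99.4% v 97.7% score above 6; power is about 11% on the cut and 91% on the full score.

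**Effect on the hypothesis as worded.** In the mean 8.0, SD 1.5 case, a true 0.5-point loss would still let the cut hypothesis be accepted in about 100 − 38 = 62% of trials.

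**The case against.** Four points on the other side have weight.

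1. A reader might infer that satisfaction is tested only as above 6 or not. The documents do not support that: the later hypothesis in section 5 and its endpoint in section 6.1 keep the full scale. A claim of higher satisfaction would rest on that hypothesis, not on the cut one.
2. A reader might infer that chi-squared is fixed for every satisfaction analysis. Section 7 leaves room for judgement, and a test for the full-scale hypothesis may stand in an analysis plan that is not shown, so its absence is no fault. The cut itself, however, is written into a hypothesis and an endpoint, and choosing a test later does not undo it.
3. A reader might infer that real losses are generally missed, or that a group falling from 9 to 7 would show no change. That holds only if no individual score drops to 6 or below. Under the model used here, a fall in group mean from 9 to 7 is detected about 100% of the time. Losses of one point are usually detected too.
4. The share above 6 is an easily understood proportion, the protocol uses thresholds elsewhere, and study success depends on the primary endpoint alone. This stands as a reason to keep reporting the share. It does not justify testing it in place of a score already in hand, with non-significance as the favourable result.

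The documents also do not say that a 0.5-point loss matters to patients; that size is an assumption.

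**Conclusion.** The point holds in limited form. One questionnaire item carries two different hypotheses with no rule for which governs. One of them rests on an unexplained cut that discards information in a setting where low power favours acceptance. For a 0.5-point loss with 100 per group, power is about 24-71% on the cut and 39-92% on the full score over the assumed range. For one-point losses the cut usually suffices. All of this depends on assumed means, SDs and a rounded normal shape; the direction was the same in every scenario run at 0.5 and 0.75 points. It concerns a secondary endpoint and leaves the primary conclusion untouched. It is worth changing because the better analysis needs no new data.

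**What to change.** - In section 5 (Secondary hypotheses) and section 6.1, make the overall 1-10 score the tested patient satisfaction endpoint. Estimate the outpatient minus regular difference in means with a 95% confidence interval, with a rank or proportional-odds analysis as sensitivity.
- Merge it with the patient part of the later full-scale hypothesis and endpoint, and state that the equal-or-higher wording governs. Judge it from the confidence interval, not from a non-significant p value. How far below zero the lower limit may lie and still count as equal has to be fixed in advance; the protocol gives no figure for this.
- Report the share scoring above 6 per group as a description.

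The cost is wording in sections 5 and 6.1, with no new data, patients or procedures. The small downside is that the share above 6 is no longer a tested result.

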#### *Discharge from hospital*

Patients in the outpatient recovery group will be released from hospital on the discretion of a nurse under supervision of a physician and return to their homes wearing the Healthdot. The Healthdot calculates and transmits heart rate, respiratory rate, posture and activity level. The physician will be able to view the values for these four parameters through a dashboard. On the dashboard, events with a heart rate above a pre-defined threshold will be flagged. A teleconsultation will be scheduled for the following morning (day 2). Before the teleconsultation, the Healthdot data will be interpreted by the physician who will then assess whether additional action is indicated. The decision based on Healthdot data is noted in the eCRF. After the teleconsultation, it is noted whether additional or

Met opmaak

Met opmaak

Tekstkleur: Au

Met opmaak

Met opmaak

|                                                                                                                    |              |                         |                  |                    |
|--------------------------------------------------------------------------------------------------------------------|--------------|-------------------------|------------------|--------------------|
| Title: Clinical Investigation Plan                                                                                 |              | Author: [name] |                  | Philips restricted |
| DocID: ICBE-2-36455                                                                                                | Version: 3.0 | Date: 2020-DEC-08       | Status: Approved | Page: 25 of 44     |
| This document is based on Philips Research Template: Clinical Investigation Plan, ID: QR-TEM-57, Date: 2019-Mar-21 |              |                         |                  |                    |

different decisions are made about the treatment based on the additional information from the teleconsultation.

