On day 3-8 the physician will check the Healthdot dashboard daily. The physician may decide to have a telephone consultation, e.g. when the Healthdot dashboard flags an event. If the physician will determine that additional action is needed (e.g. based on the information on the dashboard, or when the patient calls), in the absence of an indication from the Healthdot, such an event will be viewed as a false negative. It will be retrospectively assessed, based on the patient medical record, if false negative events have occurred. For all events flagged in the Healthdot dashboard, the physician will record whether it was a false positive notification or a true positive notification in the eCRF.

Patients in the regular recovery group will be released from hospital on the discretion of a nurse under supervision of the physician the day after surgery. For these patients no appointments outside of the regular protocol are planned.

*Table 1: Overview of protocol activities in the hospital for the two patient groups, and the differences*

| Protocol Activity for patient group
"Outpatient recovery"                                                                                                                                                                                                                                                   | Protocol Activity for patient group
"Regular recovery"                                                                                                                                                                                                                                                      | Differences                                                                                                                                        |

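### The missed-event hypothesis divides misses by notifications, so it is not a miss rate: taken alone, it can be met with every event missed if notifications are numerous enough

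*Protocol*

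**What the plan says.** The protocol addresses missed events in four places.

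- Section 5, Secondary objective(s), asks for a percentage without naming a denominator: "To evaluate the percentage of missed events (i.e. false negatives) from the Healthdot system".
- Section 5, Secondary hypotheses, defines a miss as a case where "there was no notification from the Healthdot system when the patient needed to go to the hospital" and sets the limit in the same sentence, for cases without a notification "when the patient needed to go to the hospital, are lower than 5% of all notifications". A separate hypothesis covers missed minor events, where the patient contacted the hospital but did not have to visit.
- Section 6.1 lists only a count as the endpoint: "Total number of false negative notifications from the Healthdot system".
- Section 6.4, Discharge from hospital, is broader. If the physician finds that additional action is needed "in the absence of an indication from the Healthdot, such an event will be viewed as a false negative".

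Three further statements matter. A dashboard flag is raised by heart rate alone: "events with a heart rate above a pre-defined threshold will be flagged". For each flag "the physician will record whether it was a false positive notification or a true positive notification in the eCRF". Next to the missed-event hypothesis stands a limit on false alarms: "False-positive notifications from the Healthdot system are lower than 10% of notifications per patient". Section 5 adds that the hypotheses will be accepted or rejected on the results, and that claims may be derived from primary and secondary hypotheses.

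**The concern.** A miss rate answers the question: of the events that should have triggered the monitor, what share did not? The stated ratio answers another one, because its denominator is the number of alarms. At a fixed number of misses it falls with every further notification, whether or not that notification had anything to do with a patient who needed the hospital. A more sensitive heart-rate threshold could improve the result without one more event being detected.

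The measure matters because Section 3 gives detection of short-term complications, such as bleeding, as the main reason for the overnight stay. How often the monitor misses an event requiring hospital is the most direct evidence on whether it can take over that function. A favourable verdict on a ratio driven by alarm volume could be read as such evidence.

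The definitions add to the problem. A patient who calls and needs some action short of a hospital visit can be a false negative under Section 6.4 and a missed minor event under Section 5. The objective is a percentage while the listed endpoint is a count. The same data could therefore give different answers.

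**Working it through.** The 5% is a chosen threshold with no derivation in the protocol, so there is no figure to reproduce. The check applies arithmetic to the criterion as stated.

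**Inputs.** Threshold: misses / notifications < 0.05 (Section 5). Healthdot group: 100 patients (Section 7, Sample size). Wear at home: 7 days (Section 1), hence 100 × 7 = 700 patient-days. Number of events requiring hospital, E: not given. I assume 1 to 10. The middle value of 5 borrows the complement of the 95% textbook outcome in Section 7 (5% of 100). That is only a proxy, since the textbook outcome is a 30-day composite that includes prolonged initial stay. The notification rate is not given either.

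**Step 1: every event missed.** With E misses and N notifications, the criterion is met when E/N < 0.05, that is, N > 20E.

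| Events, all missed | Smallest N that passes | Ratio | Sensitivity | Notifications per patient-day (N/700) |
|---|---|---|---|---|
| 1 | 21 | 4.76% | 0% | 0.03 |
| 2 | 41 | 4.88% | 0% | 0.06 |
| 5 | 101 | 4.95% | 0% | 0.14 |
| 10 | 201 | 4.98% | 0% | 0.29 |

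For 5 events that is 101/100, or about one notification per patient over the whole week.

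**Step 2: dependence on alarm volume.** Hold misses at 5. The ratio is 5/20 = 25%, 5/100 = 5.0% (fails), 5/101 = 4.95% (passes) and 5/700 = 0.7%, with no change in what was detected.

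**Step 3: few alarms.** With 20 or fewer notifications one miss fails, since 1/20 = 5% is not below 5%, however many events were detected. This direction matters less. If each detected event has its own notification, at most 20 were detected, and the event-based rate is at least 1/21 = 4.76%.

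**Step 4: event-based denominator.** With missed / (detected + missed) and 5 events, 5 missed gives 100% at any N, 1 missed gives 20% and none missed gives 0%.

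**Step 5: precision.** With 0 of n missed, the exact one-sided 95% upper limit is 1 − 0.05^(1/n). For n = 5 it is 1 − 0.05^0.2 = 45.1%; for n = 10 it is 1 − 0.05^0.1 = 25.9%.

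**The case against.** The strongest reply is that the criterion does not stand alone. If the 101 notifications in the example detected nothing and were recorded as false, the false-positive hypothesis would fail. Taking both limits as pooled and as jointly required, misses < 0.05N and false positives < 0.10N leave true positives > 0.90N. The event-based miss rate is then below 0.05/(0.05 + 0.90) = 5.3%, close to what was presumably intended.

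This stands only in part. The protocol nowhere requires both hypotheses to hold. The false-positive limit is worded per patient, not pooled. Above all, the 5.3% bound needs every true positive to be a detected event requiring hospital, and Section 6.4 does not say so; the classification is left to the physician. With 101 notifications, 10 false (9.9% pooled) and 91 recorded as true for matters not needing a visit, both limits are met with all 5 events missed. With none recorded as false, the false-positive limit is met under any reading and the missed-event ratio is still 4.95%.

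A second reply is that Section 6.1 speaks of false negative notifications, so misses might be meant to count within all notifications. The condition then becomes E/(N + E) < 0.05, that is, N > 19E. For 5 misses, 96 actual notifications suffice (5/101 = 4.95%). The dilution remains.

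Third, Section 6.4 may be the umbrella recording rule and Section 5 its split by need for a hospital visit. That is a fair reading, and it makes the definitional point one of clarification, but the protocol does not state it.

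**Conclusion.** The denominator is wrong as written. Taken alone, the hypothesis can be accepted at zero sensitivity whenever notifications exceed 20 times the misses. That condition follows from the stated rule and does not depend on the event rate; the worked cases rest on the assumed 1 to 10 events.

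Three stronger readings are not supported. A reader might infer that a monitor that misses everything would thereby make the trial succeed. It would not: Section 7, Pass/fail criteria, ties success to the primary endpoint alone, and the interim and stopping rules do not list missed events. A reader might infer that a product claim is settled by this ratio. Section 5 says only that claims may be derived, and Section 1 records that no list of claims exists. A reader might also infer that the trial must show an upper confidence limit below 5%, which would take at least 59 events with none missed (1 − 0.05^(1/59) = 4.95%). The protocol sets no such standard; the figure only supports descriptive reporting.

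This should be fixed as a secondary hypothesis. The primary analysis and the sample size are unaffected.

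**What to change.** - In Section 5, Secondary hypotheses, redefine the measure as missed / (detected + missed) among events in which the patient needed to go to the hospital.
- Use that one definition of a false negative in Sections 5, 6.1 and 6.4, and keep missed minor events as a separate category.
- In Section 6.1, list the percentage as the endpoint, with the count beside it.
- Report it with an exact confidence interval and treat it mainly as descriptive, because few events are expected.

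The cost is mostly wording, with one addition to data capture. Section 6.4 has the physician classify each flag as true or false, but does not link a flag to an event requiring hospital, so detected events would have to be identified from the medical record. That record is already to be reviewed for false negatives. The sponsor will probably also have to give up the below-5% claim.
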